***Missing data plan***

We anticipate the loss to follow-up will be less than 20% for the first three months. If outcome measures are missing less than 11% of participants, then the primary analysis will use a complete-case approach. If the outcome measures are missing for 11% to <20% of participants, then a sensitivity analysis using multiple imputation will be used to compute the missing outcome of the three arms.

***Ethical considerations***

IRB approval was obtained from the Dermatology Hospital of Southern Medical University (GDDHLS-20181206). All participants will be provided an online consent form prior to study initiation. This online informed consent describes what personal data will be collected, and explains that data will be used for research purposes only. Contact information will be provided for participants for further enquiry. Participants will be required to ‘click-to-consent’ and verified through mobile telephone as agreement to proceed with the study.

***Trial registration***

The study has been registered with the Chinese Clinical Trial Registry (trial ID [ChiCTR1900022409](http://www.chictr.org.cn/showproj.aspx?proj=37582)).

**Discussion**

In this study, we will test three syphilis testing models (standard of care, syphilis self-testing, and crowdsourced lottery incentivized self-testing) in a parallel randomized controlled trial. With the successful experience of HIV self-testing, we hypothesize that syphilis self-testing could increase syphilis test uptake by overcoming the structural barriers that are innate within traditional facility testing services. Findings from this study will contribute to the scarce data on the impact of syphilis self-testing on promoting routine syphilis screening among MSM. The findings will also contribute to our understanding of the safety, effectiveness and acceptability of syphilis self-testing. These findings will have important implications for self-testing policy, both in China and internationally.

Several implementation challenges that have emerged from HIV self-testing practice have limited its public health impact. Many are concerned that self-testing does not sufficiently connect users with critical post-testing services, such as confirmatory testing and management of those who test positive and that these limitations may result in delayed linkage to care [[11](#_ENREF_11), [27](#_ENREF_27), [29](#_ENREF_29), [30](#_ENREF_30)]. For syphilis self-testing, this problem could be more salient. The majority of syphilis rapid diagnostic tests detect treponemal specific antibodies. Though this has high sensitivity, it cannot distinguish past from current infections. A solution to encourage those whose self-test is reactive to undertake laboratory confirmation at the local clinic therefore needs to be developed. We have therefore introduced a new model of crowdsourced lottery incentivized syphilis self-testing, which integrates a behavioral economics tool of conditional monetary incentives enhanced by a crowdsourced approach, with the aim of enhancing syphilis testing uptake and linkage to care [[31](#_ENREF_31)]. However, the lottery prize amount, and how frequently incentives should be offered varies by populations and countries. We adopted a crowdsourcing method by organizing an opening contest from the target community to inform design an optimized financial incentive model in helping delivery of syphilis testing service (include self-testing) and linkage to care [[25](#_ENREF_25), [32](#_ENREF_32), [33](#_ENREF_33)]. This is a major innovation of this study and, if successful, it will provide insights to inform design of optimal self-testing model by using crowdsourcing method and tools of behavioral economics.

The major challenge of this study is to retrieve validated testing proof to verify self-testing results. Our previous study reported that 47% of men submitted proof of syphilis self-testing with 20 RMB (about 3 US dollar) cash incentive [[18](#_ENREF_18)]. This was a cross sectional survey, and people are not always able to find the required proof, especially for those who tested a long time ago. Furthermore, we cannot guarantee that submitted photographic proofs truly belongs to the patient. We previously found that more than 30% of men would submit a proof of testing even if no incentive was offered in an HIV self-testing study [[25](#_ENREF_25)]. To increase the retrieval rate, we will provide a small cash incentive (5 RMB) to reimburse their submission of self-testing results or other testing proof materials. To link self-test kits with the user, we will code each self-testing package and direct them to take a photo of the used strip with the background of the package, which has been successfully tested in our pilot trial.

Another potential limitation of this study is the possibility of contamination between arms. We cannot prevent participants from the control arm to purchase syphilis self-testing kits for use through online e-market which we have been previously found in some MSM in China [[18](#_ENREF_18)]. To mitigate this, we will record the participants’ testing method in each group and if necessary adjust for this in the data analysis. The six-month duration of follow-up also limits the ability of the study to assess the long-term effect of the intervention on syphilis incidence.

Findings from this proposed study will be used to inform the design of a new syphilis self-testing model, which will be implemented alongside the traditional facility-based testing service to increase syphilis screening among MSM in China. We anticipate that the model will increase early syphilis diagnosis and enhance syphilis continuum of care and treatment for MSM, and ultimately reduce the spread of syphilis and HIV transmission among MSM and other individuals within their sexual networks in China.

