**Arms and Interventions**

Arms and interventions are summarized in Table 1.

**1. Control arm:** Participants in the control arm will be provided information about local STD services and encouraged to uptake free syphilis testing at their local STD or HIV voluntary testing and counseling (HTC) clinics. HTC clinics in China provide both HIV and syphilis testing free of charge. Participants will be encouraged to screen for syphilis every three months. Reminder will be sent by SMS or WeChat (a social media app like Twitter and Facebook, commonly used in China) three monthly (enrollment, three-month, and six-month) during six months study period.

**2. Standard self-testing arm**: In addition to being prompted to uptake syphilis testing at local facilities, participants in this arm will be provided with access to syphilis self-testing along with the reminders. Participants may request order of syphilis self-testing packages through WeChat with the package being sent to participants by postal mail (express delivery). The provision of syphilis self-testing service will last for six months. Participants order self-testing package online with maximum oneself-testing package per month.

**3. Lottery incentivized self-testing arm**: In this arm, the participant will be provided with both control arm and standard syphilis self-testing arm interventions. In addition, participants who confirm that they have tested for syphilis during the trial period either through self-testing or facility-testing will be given a lottery draw. The lottery draw will provide a 10% chance of winning 100 RMB (equal to 15 US Dollars). The procedure, value and probability of the lottery scheme was determined by a previous open crowdsourcing contest. We solicited 14 lottery schemes via an open crowdsourcing contest. The winning entries were then used to develop the aforementioned lottery incentivizes to be used in the current study.

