**Outcomes Measures**

The primary outcome is the proportion of participants who tested for syphilis during the trial. Syphilis tests may be either at a clinic or via self-test. This will be verified in all participants using photo-verification. We will additionally look at the incremental benefit of the lottery incentive efficacy in promoting syphilis, number of newly identified syphilis infections, the linkage to syphilis clinical care after self-testing, the proportion of HIV and other STIs (chlamydia, gonorrhea) tests among the participants who use self-testing and cost-effectiveness of syphilis self-testing in promoting uptake of syphilis testing among Chinese MSM.

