**Surveys**

**Baseline:** All participants complete a self-administered survey on an online survey platform (Wen Juan Xing, https://www.wjx.cn) at enrolment. The baseline survey includes questions on socio-demographic characteristics, sexual behaviors, past HIV/syphilis testing and treatment, and attitude towards syphilis self-testing.

**Follow-up surveys:** Participants in the three arms of the study will complete a brief online survey at three-monthly intervals. The follow up surveys collects information on the number, time, location, reasons for, and results of syphilis tests (including self-tests) and other STI tests at clinics and community sites, and sexual risk behaviors in the past three months. Participants in the two self-testing arms are also asked about the number of self-test kits they used to test their sexual partner(s) or if they gave any kits to someone else to test. At the last follow-up, participants will be asked to get STD (HIV, syphilis, chlamydia, and gonorrhea) screening test in their nearby clinic. The testing fee will be redeemed by an upload of the test results. Participants will be provided with 30 RMB (equal to 4 US Dollars) for their time to complete each follow-up survey.

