#### *Analysis plan*

Data will be retrieved from the online survey platform. De-identified datasets and codebook will be stored for statistical analysis. The syphilis testing proportion in each arm (control, standard self-testing, and lottery incentivized self-testing) will be assessed using an intention-to-treat analysis during the follow-up period, excluding confirmatory tests after a reactive self-test.

The effects of the intervention will be measured by comparing the differences in proportions of men who take syphilis testing during two rounds of follow up by using generalized estimating equation (GEE) model. We will use the chi-square test to compare differences in the proportion of linkage to syphilis clinical care, have HIV and other STI (chlamydia, gonorrhea) testing performed, and have condomless sex events with different partners within six months of randomization across three groups and use post-host test to check the significance of differences between each of the two groups.

We will estimate the total and incremental unit costs for each arm. All costs will be identified as start-up costs, fixed costs and variable costs. Start-up costs are incurred during the process of creating this study (e.g. survey platform coordination). Fixed costs are costs that do not change with an increase or decrease in the number of people served during the trial period (e.g. administration, office equipment). Variable costs are expenses that vary with the number of participants served (e.g. recruitment, supplies, postage fee). We will first calculate the total cost for each group, then divided these costs by the number of men tested and the number of newly identified syphilis cases detected in each study arm to obtain the incremental unit costs. In addition, we will build a decision tree model using a healthcare provider perspective to estimate the incremental cost for per additional person tested and case identified for each intervention will be calculated. Univariate, multivariate and probabilistic sensitivity analyses will be conducted to test the robustness of our results.

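### The Discussion allows adjustment for testing method, which is a post-randomisation part of the outcome; as a covariate it would distort the intention-to-treat effect and would not correct contamination

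*Protocol*

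**What the plan says.** The Protocol's Discussion names contamination as a limitation: "We cannot prevent participants from the control arm to purchase syphilis self-testing kits" online. As mitigation, it says the trial will record participants' "testing method in each group and if necessary adjust for this in the data analysis". It does not say what would make adjustment necessary, how it would be done, or whether it belongs to the primary or a secondary analysis.

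The passages this touches are:

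- **Outcomes Measures:** "The primary outcome is the proportion of participants who tested for syphilis during the trial", and "Syphilis tests may be either at a clinic or via self-test".
- **Arms and Interventions:** control participants get information and reminders about free facility testing. In the standard self-testing arm, "participants in this arm will be provided with access to syphilis self-testing along with the reminders".
- **Data collection and Surveys:** whether, where and how a man tested is learned from uploaded photographs and from the three-monthly follow-up surveys, all after randomisation.
- **Analysis plan:** the testing proportion in each arm "will be assessed using an intention-to-treat analysis during the follow-up period". The intervention effect compares proportions tested "during two rounds of follow up by using generalized estimating equation (GEE) model". No covariates are named.

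**The concern.** A covariate in a randomised comparison should be fixed before allocation. Testing method fails this in three ways.

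1. It is measured during follow-up and can be changed by the allocated arm.
2. It is part of the outcome. It exists only for men who tested, and every man who self-tested has the outcome by definition.
3. It is the mechanism. What the standard self-testing arm adds to control is access to self-tests, so holding self-testing constant removes much of what the trial sets out to measure.

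Nor does it serve its stated purpose. Control men who buy kits raise the control proportion and so can only dilute the intention-to-treat difference. A correction should move the estimate up or leave it alone, whereas conditioning on method generally moves it down. At stake is a real benefit of offering self-tests being reported as small, absent or reversed.

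**Working it through.** **Inputs.** Protocol, Sample size: pilot proportions tested 0.36 (control) and 0.74 (self-testing), 80% power, type I error 0.05, 20% loss, 29 per arm. The Protocol does not report how tests divide between self-test and facility within arms. Two shares are therefore assumptions: f, the share of control-arm tests that are self-tests, and g, the same share in the standard self-testing arm.

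**The plan's own figure.** Two-sided, unpooled variance:
n = (1.960 + 0.842)² × (0.36×0.64 + 0.74×0.26) / 0.38² = 7.849 × 0.4228 / 0.1444 = 23.0; 23.0/0.80 = 28.7, rounded up to 29. This matches, so 0.74 versus 0.36 is the planning contrast. It is a difference of +0.38 and an odds ratio of (0.74/0.26)/(0.36/0.64) = 5.06.

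**Coding none/facility/self.** The outcome is 0 for none and 1 for the other two levels. The covariate determines the outcome completely. With an identity link the arm coefficient is zero; with a logit link there is complete separation and it cannot be estimated.

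**Coding self-test yes/no.** Let s_c = 0.36f and s_t = 0.74g. Among self-testers the outcome is 1 in both arms, a difference of 0. Among the rest:

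- control: c₀ = (0.36 − s_c)/(1 − s_c)
- self-testing: t₀ = (0.74 − s_t)/(1 − s_t)

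The additive linear model weights the two strata by w₀ = (1−s_c)(1−s_t)/[(1−s_c)+(1−s_t)] and w₁ = s_c·s_t/(s_c+s_t), so the adjusted difference is w₀(t₀ − c₀)/(w₀ + w₁).

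Example, f = 0.25 and g = 0.7: s_c = 0.09, s_t = 0.518; c₀ = 0.27/0.91 = 0.297; t₀ = 0.222/0.482 = 0.461; w₀ = 0.315, w₁ = 0.077; adjusted difference = 0.315 × 0.164/0.392 = +0.13.

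Adjusted risk difference (unadjusted: +0.38):

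| | g = 0.5 | g = 0.7 | g = 0.9 | g = 1.0 |
|---|---|---|---|---|
| f = 0 | +0.23 | +0.10 | −0.14 | −0.36 |
| f = 0.1 | +0.23 | +0.11 | −0.10 | −0.29 |
| f = 0.25 | +0.24 | +0.13 | −0.06 | −0.21 |
| f = 0.5 | +0.27 | +0.17 | 0.00 | −0.13 |

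**Where the sign changes.** Among men who did not self-test, the odds ratio is 5.06 × (1−g)/(1−f). It reaches 1 at g = 1 − (1−f)/5.06, which is 0.80 for f = 0, 0.85 for f = 0.25 and 0.90 for f = 0.5.

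**Odds-ratio scale.** The same expression shows that the odds ratio shrinks only when g exceeds f. At f = g = 0.5 it stays at 5.06, although the risk difference falls to +0.27. That corner needs facility testing of 0.74×0.5 = 0.37 in the self-testing arm against 0.36×0.5 = 0.18 in control, an unlikely pattern when the added service is self-test kits.

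**Does it correct contamination?** With f = 0 there is no contamination and a correction should leave +0.38 unchanged; adjustment gives +0.23 to −0.36. With f = 0.25, 0.09 of control men self-tested. If all of them would otherwise have tested at a facility, the uncontaminated difference is 0.38; if none would, it is 0.74 − 0.27 = 0.47. Adjustment gives +0.24 to −0.21, outside that range and on the wrong side.

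**The case against.** The clause sits in a limitations paragraph of the Discussion. The operative text is the Analysis plan, which specifies intention-to-treat and names no covariates. A reader might infer that the plan commits to replacing that analysis with an adjusted one; the Protocol does not say so, and an unadjusted primary analysis is compatible with everything written. The wording can also be read as adjusting for contamination rather than entering method as a regression covariate, and that reading could include a legitimate complier-average analysis. The trigger and details of a contingency analysis are commonly left to an SAP, so their absence alone is no finding.

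A reader might also infer that adjustment would necessarily abolish or reverse the effect, or that the model would fail to fit. Neither is established. With a yes/no covariate and 50–70% of self-testing-arm tests being self-tests, the difference stays positive. Reversal needs roughly 80–90%, and the Protocol reports no such shares. Failure to fit applies to a three-level coding with a logit-type link, and no link is named.

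Finally, the Protocol itself treats purchased kits as contamination and sets the comparison against facility-based testing, so wanting a supplementary contamination-free estimate is reasonable.

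All of this stands, and it limits severity. It does not remove the point: the nearest reading of the sentence is adjustment for testing method, that adjustment is wrong for the stated effect, and nothing keeps it out of the primary analysis.

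**Conclusion.** The point holds as a should-fix. The Protocol permits, without confining it to a sensitivity analysis, an adjustment that would not estimate its own intention-to-treat effect and would not repair contamination.

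On the risk-difference scale, attenuation of the +0.38 pilot difference appears in every scenario tried. Removal or reversal is conditional on a high self-test share in the self-testing arm or on a three-level coding. These results rest on the pilot rates carrying over to the trial, on assumed self-test shares, and on an additive linear model for the yes/no covariate. The direction of the sign change does not depend on choosing a difference or an odds ratio.

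**What to change.** 1. In the Discussion, delete the clause that allows adjustment, keeping the commitment to record testing method.
2. In the Analysis plan, add one sentence: the primary intention-to-treat contrasts are not adjusted for testing method or any other variable measured after randomisation.
3. Report self-test and facility testing descriptively by arm, including control-arm use of purchased kits.
4. If a contamination-corrected estimate is wanted, pre-specify it as a secondary complier-average analysis with randomised arm as the instrument for self-test use. Limit it to standard self-testing versus control: the lottery also rewards facility testing (Arms and Interventions), so in that arm allocation can change the outcome other than through self-testing. Even in the standard arm, the analysis should state the assumption that offering kits changes testing only through their use.

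The cost is wording only. The follow-up surveys and photo verification already collect the information needed; sample size and procedures do not change.
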